### Phase II: trial deployment

#### Setting

The trial will be implemented in PHC centres across the province of Mendoza, Argentina, which serve approximately 45% of the population, primarily individuals from socioeconomically disadvantaged backgrounds. The province is administratively divided into 18 departments. The unit of randomisation (cluster) will be the department. 12 departments will be selected, each contributing at least two PHC centres. Clusters will include two or three PHC centres providing care to ≥50 individuals diagnosed with T2D per cluster. Centres involved in the pilot phase will be excluded from phase II.

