#### Sample size

Based on preliminary data from the diagnostic phase and published literature, the baseline rate of achievement for the composite primary outcome (glycaemic control (HbA1c <8%); blood pressure control (<140/90 mm Hg); and use of statins (statin prescription) -limited to patients ≥40 years-) in the control group is estimated at 30%. The intervention is expected to improve this to ≥50% (absolute effect size of 20%). We have calculated the sample size considering a parallel cluster randomised trial with a cohort design, including baseline and follow-up assessments. The trial is powered at 80% to detect an absolute difference of 20 percentage points between the control group (30%) and the intervention group (50%) on the composite primary outcome, assuming a two-sided significance level of 5%. The design includes six clusters per arm (12 in total) and accounts for the correlation structure of repeated measures using a two-period decay model. Specifically, we assumed an intracluster correlation coefficient (ICC) of 0.05, a cluster autocorrelation of 0.5, and an individual autocorrelation of 0.6. Standard errors were adjusted using a t-distribution to account for the small number of clusters. Based on these parameters, the required sample size before adjusting for attrition is 312 individuals (26 per cluster). Applying an attrition inflation factor of 1.25 (to allow for 20% loss to follow-up), the final sample size increases to 396 individuals (33 per cluster, 198 per arm).

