#### Data analysis

We will use all available data from all randomised clusters and conduct all analyses on the intention-to-treat (ITT) population, including all clusters and patients in the randomised group, regardless of intervention adherence. Summary statistics will be given for baseline data by treatment group using means, SD, medians, minimum, maximum and quartiles for continuous variables and counts and percentages for categorical variables. We will quantify complete vs incomplete records and describe the characteristics of patients lost to follow-up.

For the composite clinical outcome, the primary ITT analysis will compare the proportion of patients achieving an HbA1c level <8%, blood pressure control <140/90 mm Hg and statin uptake between the trial arms at the end of the study. We expect a good covariate balance between the groups; therefore, the ITT analysis will be performed by comparing proportions. Patient and cluster-level covariates can be included in a mixed-effects logistic regression model to account for the cluster effect and obtain an adjusted estimate of the average treatment effect for within-cluster change.^35^ Adjusted ORs will be reported with 95% CIs, p values and ICCs will be reported to estimate the percentage of variance explained by each level.

For quality of care, we will compare the proportion of patients reporting overall quality of care as ‘excellent’ or ‘very good’ before and after the intervention phase between trial arms using difference-in-difference regression analysis to estimate the average treatment effect. Engagement and confidence in the health system will be evaluated by comparing the proportion of patients achieving the expected threshold in each trial using a χ^2^ test for proportions. Fisher’s exact test will evaluate system competence across participating PHC centres. Direct costs related to diabetes care will be reported for each group. We may expect higher costs in the intervention group due to increased and better utilisation of health services. The mean cost will be analysed considering the variable distribution (non-normal/normal). For all outcomes, we will conduct mixed effects regression adjusted for covariates and clustered by department to provide an average treatment effect for expected change in outcomes within each department.

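### The primary analysis is named as a comparison of proportions although departments are randomised, and the protocol never says whether this or the clustered model decides

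*Protocol article*

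**What the plan says.** On design, the Setting section states: "The unit of randomisation (cluster) will be the department". The Sample size section is built on that: "The design includes six clusters per arm (12 in total) and accounts for the correlation structure of repeated measures using a two-period decay model". It assumes an ICC of 0.05, a cluster autocorrelation of 0.5 and an individual autocorrelation of 0.6, and adds: "Standard errors were adjusted using a t-distribution to account for the small number of clusters".

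On analysis, the Data analysis section names the arm comparison of the composite at the end of the study as the primary ITT analysis and continues: "We expect a good covariate balance between the groups; therefore, the ITT analysis will be performed by comparing proportions". The clustered model follows as a possibility: "Patient and cluster-level covariates can be included in a mixed-effects logistic regression model to account for the cluster effect". Adjusted odds ratios with confidence intervals and p values are to be reported.

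For secondary outcomes, the key one (user-reported quality of care) is analysed by difference-in-difference regression. For two others: "Engagement and confidence in the health system will be evaluated by comparing the proportion of patients achieving the expected threshold in each trial", by a chi-square test. For system competence, Fisher's "exact test will evaluate system competence across participating PHC centres". The paragraph ends by promising, for all outcomes, covariate-adjusted mixed-effects regression clustered by department.

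**The concern.** The stated reason does not support the method. Balance on covariates bears on confounding and precision. It does not make patients of one department independent of each other, and that dependence governs the standard error here. With 12 randomised units, a test that treats 312 or 396 patients as independent overstates the information in the data.

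The analysis also does not match the sizing, which allows for clustering, for the baseline measurement and for the small number of clusters. The comparison named as primary is tied to none of these. Because a clustered model is promised as well, the primary outcome can end with two results and no rule for which one counts.

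The stakes are practical. Control departments are to be offered the package if it proves effective, and the findings are meant to inform provincial policy. A nominally significant unclustered result would be weak support for either.

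**Working it through.** **Inputs.** All from the Sample size section unless noted: 6 departments per arm; m = 26 per department before attrition, 33 after; ICC 0.05; cluster autocorrelation (CAC) 0.5; individual autocorrelation (IAC) 0.6; 30% against 50%; two-sided 5%. The Data analysis section counts missing clinical outcomes as failures, so all 33 enrolled per department enter the primary analysis.

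**1. Reproducing the stated sample size.** Design effect DE = 1 + (m − 1) × ICC. Correlation of baseline and follow-up cluster means r = [m × ICC × CAC + (1 − ICC) × IAC] / DE. For a baseline-adjusted analysis, SE = √{[p1(1 − p1) + p2(1 − p2)] × DE × (1 − r²) / (6m)}.

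At m = 26:
- DE = 1 + 25 × 0.05 = 2.25
- r = (0.65 + 0.57) / 2.25 = 0.542, so 1 − r² = 0.706
- SE = √(0.46 × 2.25 × 0.706 / 156) = 0.0684
- 0.20 / 0.0684 = 2.92

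Power by reference distribution:

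| Analysis | m | Reference | Power |
|---|---|---|---|
| Baseline-adjusted | 26 | t, 20 to 22 df | 79.4–79.7% |
| Baseline-adjusted | 26 | t, 10 df | about 75% |
| Baseline-adjusted | 33 | t, 10 df | 78.5% |
| End-of-study only | 26 | t, 10 df | 59–60% |
| End-of-study only | 26 | normal | 69% |

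The stated 80% is reproduced by a clustered, baseline-adjusted analysis with a t reference on about 20–22 df. Attrition: 26 / 0.8 = 32.5, rounded up to 33; 33 × 12 = 396, as stated.

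**2. Type I error of an unclustered comparison.** The true variance is DE times the assumed one, so the standard error is too small by a factor √DE (1.50 at m = 26, 1.61 at m = 33), and true α = 2 × [1 − Φ(1.96 / √DE)].

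| ICC | m = 26 | m = 33 |
|---|---|---|
| 0.05 (protocol) | DE 2.25, α 19.1% | DE 2.60, α 22.4% |
| 0.01 (assumption) | 8.0% | 8.8% |
| 0.02 (assumption) | 11.0% | 12.6% |
| 0.10 (assumption) | 29.5% | 33.9% |

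Beta-binomial simulation at ICC 0.05 and a 30% rate agrees: about 19% and 22–23%. A continuity-corrected chi-square gives about 16.5% and 20%. A t-test on department proportions with 10 df gives 5.0%.

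**3. Restricted randomisation.** These figures assume simple allocation. As an illustration, suppose allocation were drawn from the 10% of allocations best balanced on the baseline composite itself. With r about 0.54, the error falls to about 12% (m = 26) and 15% (m = 33). The protocol balances on baseline HbA1c, sociodemographic factors and cluster size, not on the composite, so the true reduction is unknown.

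**4. Fisher's test.** System competence is defined per site, with 24–36 sites (12 departments × 2–3). Simulated error is about 2–3.5% at a site-level ICC of 0.05, 3–6% at 0.2 and 5–12.5% at 0.5. All three ICCs are assumptions.

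**The case against.** The strongest reply is that the protocol does commit to a department-clustered mixed model for every outcome, and that the only inferential output it details for the composite, adjusted odds ratios with intervals and p values, comes from that model. No test is named for the comparison of proportions, which could be meant as descriptive. This stands in part: the inflated error is conditional on the simple comparison being decisive. It does not remove the problem, because the simple comparison is the one tied to the primary ITT analysis and nothing says that the model supersedes it.

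Two stronger readings are tempting.
- A reader might infer that the 19–22% error applies to all the simple tests. It does not. The ICC of 0.05 is stated for the composite, and none is given for engagement or confidence. Fisher's test works on centres, where the patient-level design effect does not apply and the test can be conservative. The key secondary outcome uses neither test.
- A reader might fault the mixed model for lacking a small-sample reference distribution. Alone, that is detail that an article may leave to the analysis plan, and the sizing shows that the team knows the issue.

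It is also fair that restricted randomisation may bring the error below 19–22%. In the favourable illustration above it is still 12–15%.

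**Conclusion.** The point holds for the primary outcome. The protocol justifies a comparison of proportions by covariate balance, which does not address clustering, and leaves open which of two analyses decides. If the unclustered comparison decides, the two-sided type I error is about 19% (26 per department) to 22–23% (33 per department, the relevant case). This rests on the protocol's own ICC of 0.05, equal department sizes and balancing factors that do not predict the outcome. At an ICC of 0.01 it is 8–9%.

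The chi-square tests for engagement and confidence have the same flaw, of unknown size. Fisher's test ignores the nesting of centres in departments, but no inflation of this order can be claimed for it.

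**What to change.** In the Data analysis section, name one decisive primary analysis. It should account for department, adjust for the baseline composite outcome to match the baseline-and-follow-up design that was sized, and carry the small-sample t correction already used there. A cluster-level analysis, or a permutation test over the allocations that the restricted randomisation allows, would also serve. Remove the covariate-balance justification and make the simple proportions descriptive. For the binary secondary outcomes, make the department-clustered model already promised the inferential analysis in place of chi-square, and state how nesting within departments is handled for system competence.

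The cost is wording and wider confidence intervals, with no new data. Baseline adjustment should not be left out: on 10 df at 26 per department, an end-only clustered analysis has about 59–60% power, against about 75% with adjustment. Even adjusted, 10 df gives about 75% (26 per department) or 78.5% (33), so the stated 80% should be checked against the degrees of freedom chosen.

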#### Randomisation procedures

Clusters will be randomly assigned in a 1:1 ratio to the intervention or control arm following completion of baseline data collection. A restricted randomisation approach will be used to ensure balance across arms with respect to baseline HbA1c levels, key sociodemographic characteristics (such as age, sex, income and education), and cluster size. These parameters will be used to guide the allocation process to maintain equivalence across study arms, thereby strengthening the internal validity of the research. Should any residual imbalances arise post-randomisation, we will adjust for these covariates in the statistical analyses.

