#### Outcomes

The primary outcome will be a composite outcome including glycaemic control (HbA1c <8%); blood pressure control (<140/90 mm Hg); and use of statins (statin prescription) limited to patients ≥40 years. The source to obtain this data will be routine clinical records.

Secondary outcomes measured through participant questionnaires include user-reported quality of care (key secondary outcome), PHC engagement, system competence, patient confidence in the health system, inequities in outcomes and patient empowerment. User-reported Quality of Care is the overall rating of quality of care from enrolled patients, categorised as ‘excellent or very good’ versus ‘good’ or worse. PHC engagement is measured as the percentage of visits conducted at the PHC level during the data collection period, with positive engagement defined as ≥75% of all non-urgent ambulatory visits.^31^ System competence is defined as ≥75% of enrolled patients per site adhering to the complete set of selected diabetes prevention recommendations from national and provincial guidelines: annual eye exam, yearly foot exam, annual kidney function assessment, annual blood pressure measurement and biannual HbA1c measurement during the follow-up period. Patient confidence in the health system is measured by the combination of three aspects in the e-Cohort survey: health security, endorsement of the current system and trajectory.^32^ Security: We will calculate the percentage of respondents answering ‘somewhat’ or ‘very confident’ to ‘How confident are you that you would receive good quality healthcare if you became very sick?’ and ‘that you could afford the healthcare you needed if you became very sick?’. Confidence: The proportion of respondents indicates that in the past 2 years, the health system has been improving (vs staying the same or getting worse). Endorsement is indicated by agreement that the system works well and needs only minor reforms (vs significant changes needed or need to be completely rebuilt). To assess inequities, we will explore gender, migration status, education and income as potential variables related to underperformance in primary outcomes. Finally, we will measure patient empowerment using the Diabetes Empowerment Scale. This instrument is free and easy to use and has been adapted and validated in its Spanish version.^33^

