#### Data collection

We will construct a longitudinal cohort of patients with T2D in both arms, enrolling patients before implementation and following them for 12 months for outcome assessment and an additional 6 months for sustainability assessment. Our methodology builds on the e-Cohort framework that we previously optimised and used for this context at the provincial level.^34^ Participants will be contacted via telephone or in person at the PHC centre for eligibility assessment. If eligible, they will have their first in-person visit at their PHC centre, during which informed consent will be requested for recruitment (onlinesupplemental materials A  B). For all consenting patients, we will extract data about patient visits and laboratory testing from routine clinical records and costs from administrative databases for all participating facilities. During the first visit, we will administer a baseline questionnaire. Subsequently, we will conduct quarterly telephone surveys and conclude with an endline questionnaire in person at the end of the intervention period. We will implement a standardised clinical electronic data collection system using REDCap for all study data collection phases. The research team will collect monitoring data from participating facilities throughout the trial. This includes attendance at QILN activities (total attendance and sustained participation by initial team members), team meetings within each facility, timely submission of implementation team reports and implementation checklists completed quarterly during the study team observations. Specially trained data collectors will perform daily data processing at each participating PHC centre.

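### Difference-in-differences for the key secondary outcome gives up precision that adjusting for the patient's own baseline rating would keep

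*Protocol article*

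**What the plan says.** - **Status of the outcome.** The Outcomes section lists "user-reported quality of care (key secondary outcome") among the questionnaire measures, dichotomised as the top two ratings against the rest.
- **Named analysis.** Under Data analysis, the proportion giving a top-two rating is compared "before and after the intervention phase between trial arms using difference-in-difference regression analysis to estimate the average treatment effect". No reason is given for this choice.
- **Baseline data.** Under Data collection, the same cohort is surveyed before and after: "During the first visit, we will administer a baseline questionnaire", and there is an in-person endline questionnaire.
- **Order of events.** Under Randomisation procedures: "Clusters will be randomly assigned in a 1:1 ratio to the intervention or control arm following completion of baseline data collection".
- **Correlations.** The Sample size section gives an ICC of 0.05, "a cluster autocorrelation of 0.5, and an individual autocorrelation of 0.6". These belong to the primary clinical composite. Nothing comparable is given for the quality rating.
- **General sentence.** The same Data analysis paragraph ends by promising, for every outcome, a covariate-adjusted mixed-effects regression that allows for department. It does not name the baseline rating as a covariate.

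**The concern.** Difference-in-differences is designed for groups that may differ systematically at the start. Here allocation follows baseline, so the expected baseline difference is zero and whatever is observed is chance. Subtracting it in full fixes the baseline slope at 1. The efficient weight is the baseline-to-endline correlation, which is below 1. The excess weight brings baseline noise into the estimate.

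With only 12 clusters precision is scarce, and this is the secondary outcome that the plan ranks highest. If the rating is only moderately stable over time, the chosen method can be less precise than leaving the baseline rating out altogether.

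**Working it through.** **Inputs** (Protocol article, Sample size): six clusters per arm; m = 26 per cluster before attrition; ICC 0.05; cluster autocorrelation (CAC) 0.5; individual autocorrelation (IAC) 0.6; "absolute difference of 20 percentage points between the control group (30%) and the intervention group (50"%); two-sided 5%. Applying these to the quality rating is an assumption.

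**1. Correlation of a cluster's baseline and endline means**

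r = [m·ICC·CAC + (1 − ICC)·IAC] / [1 + (m − 1)·ICC] = (0.65 + 0.57) / 2.25 = 0.542

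**2. Endline-only variance of the difference in proportions**

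[0.3×0.7 + 0.5×0.5] × 2.25 / (6 × 26) = 0.46 × 2.25 / 156 = 0.00663

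**3. Variance factors relative to endline-only**

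- Difference-in-differences: 2(1 − r) = 0.916; SE √(0.00663 × 0.916) = 0.0779.
- Baseline-adjusted or constrained baseline: 1 − r² = 0.706; SE 0.0684.
- Ratio: 0.916 / 0.706 = 2/(1 + r) = 1.30.

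**4. Reproducing the plan's own figure.** The 312 is for the primary outcome. With factor 1 − r² and t on 24 df (the article does not state the df), the smallest m with 80% power is 26, so N = 312; power is 80.0%. Attrition: 26 × 1.25 = 32.5, rounded up to 33, × 12 = 396. The formula and inputs therefore match the plan's. With the difference-in-differences factor on the same 24 df, power at m = 26 is 69%, and 69 per cluster would be needed.

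**5. Does the gain survive 12 clusters?** The factor 1 − r² treats the slope as known.

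- *Patient-level baseline rating only.* The slope is estimated from some 312 patients, so estimating it costs little. With a within-cluster slope of 0.6 the factor is 1 + 0.6² − 2×0.6×0.542 = 0.709, and the ratio is 0.916 / 0.709 = 1.29. Simulations with 12 clusters of 26 gave about 1.3 for a continuous outcome, and about 1.4 for a binary one with correlations assumed on a latent scale.
- *Cluster baseline proportion as well.* A second slope must come from 12 clusters. This inflates variance by about (12 − 3)/(12 − 4) = 9/8 and uses one df: 0.706 × 9/8 = 0.794, SE 0.0726, ratio 0.916 / 0.794 = 1.15. Simulations adjusting for cluster means only gave 1.15 to 1.16 (continuous), and 1.10 or 1.27 (binary, depending on the latent correlations assumed).

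**6. Illustrative power for 30% v 50%** (noncentral t)

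| Analysis | SE | df | Power |
|---|---|---|---|
| Difference-in-differences | 0.0779 | 10 | 64% |
| Adjusted, cluster slope also estimated | 0.0726 | 9 | 69% |
| Adjusted, slope treated as known | 0.0684 | 10 | 75% |

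**7. Sensitivity to the unknown correlation**

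- The large-sample ratio 2/(1 + r) runs from 1.67 at r = 0.2 to 1.05 at r = 0.9.
- Since 2(1 − r) exceeds 1 when r < 0.5, difference-in-differences is then less precise than endline-only. For example, IAC 0.3 (assumption) gives r = 0.416 and a factor of 1.17. The ratio to the adjusted analysis is 1.41, or 1.26 with the 9/8 inflation.
- If the cluster slope is estimated, difference-in-differences becomes the more precise once 2/(1 + r) falls below 9/8, that is, r above about 0.78.

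**The case against.** **Difference-in-differences is a recognised, pre-stated and unbiased method, so preferring another is a matter of taste.** The first part stands. A reader might infer that the treatment effect on this outcome will be biased or invalid. The documents do not support that: under randomisation the expected baseline difference is zero and both estimators are centred on the same risk difference. But one of two valid methods uses data already collected less well, and no offsetting benefit is claimed.

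**The paragraph already promises covariate-adjusted mixed models for all outcomes.** This softens the point. A covariate list may well sit in a fuller document. The sentence nonetheless does not name the baseline rating, describes its target as change within departments, and does not replace the method assigned to this outcome.

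**The size is borrowed and depends on the model.** This stands. The rates and correlations are those of the clinical composite. It would also be too strong to say that difference-in-differences always loses by 2/(1 + r): that formula treats the slope as known. With a cluster-level slope estimated from 12 clusters the loss is about half as large, and it reverses at high correlations.

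**On an odds-ratio scale the two analyses may not estimate the same quantity.** This stands too. Conditioning on the patient's baseline rating changes the meaning of an odds ratio for a binary outcome, so the effect measure must be fixed.

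**Conclusion.** The point holds as one of efficiency, not validity. At the primary outcome's correlations, difference-in-differences has about 1.3 times the variance of an analysis adjusted for the patient's own baseline rating, and about 1.15 times if a cluster-level slope is estimated as well. Illustrative power is about 64% against roughly 69% to 75%. The direction is secure for patient-level adjustment at moderate correlations. The size is conditional, because the article gives no rate, correlation or target difference for the rating.

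Two further inferences should not be drawn. The trial does not miss a stated power for this outcome, since none is claimed. Nor does the method contradict the sample size: the 312 reproduces with a baseline-adjusted variance, but it was calculated for the primary composite and says nothing about how the rating is to be analysed.

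**What to change.** Under Data analysis, make the main analysis of user-reported quality of care one of the following:

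- a cluster-adjusted model of the endline rating with arm and the patient's own baseline rating; or
- a constrained-baseline repeated-measures model.

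Report a risk difference, or a marginal standardised difference if the model is logistic, so that the estimand is unchanged. Apply a small-sample correction for 12 clusters. Leave out the cluster's baseline proportion or treat it as optional, because it costs a degree of freedom among 12 clusters. Keep difference-in-differences as a sensitivity analysis.

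The cost is a change of wording. The baseline questionnaire is already planned, and neither the data collection nor the sample size changes.

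### PHC engagement and confidence in the health system are assigned a patient-level chi-square test although departments are randomised, and the plan does not say whether this test or the clustered mixed model decides

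*Protocol article*

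**What the plan says.** Setting (protocol article): "The unit of randomisation (cluster) will be the department".

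Sample size: six departments per arm, with an "intracluster correlation coefficient (ICC) of 0.05, a cluster autocorrelation of 0.5, and an individual autocorrelation of 0.6", and a t-distribution to allow for the small number of clusters. These values are given for the primary composite only.

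Data analysis: engagement and confidence are evaluated by the proportion of patients "achieving the expected threshold in each trial using a χ^2^ test for proportions". No adjustment for department is named for this test. The paragraph closes with a general statement: "For all outcomes, we will conduct mixed effects regression adjusted for covariates and clustered by department", giving an effect on expected change within department.

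Outcomes: engagement is a share of visits over the data collection period, positive at 75% or more. Confidence comes from survey items. Neither is the key secondary outcome, which is user-reported quality of care.

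**The concern.** A chi-square test of two proportions takes its variance from independent patients. Patients in one department share clinics, appointment systems and access to secondary centres, so their use of PHC and their view of the system may well be correlated. The arms then differ by chance more than the test allows, and it rejects too often.

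The authors expect clustering: the sample size allows for an ICC and for only 12 clusters. The test named for these two outcomes does not follow that reasoning.

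The closing sentence on mixed models adds a second analysis without ranking the two. Each outcome could therefore end up with two p values of different validity and no rule for choosing between them. Engagement and confidence bear on the part of secondary objective (c) that concerns service use patterns and user confidence, and the results are meant for policymakers.

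**Working it through.** **Inputs.** From Sample size: 6 departments per arm; 26 patients per department before the attrition allowance and 33 after it; two-sided 5%; ICC 0.05, cluster autocorrelation (CAC) 0.5 and individual autocorrelation (IAC) 0.6, all for the composite; 30% versus 50%. Assumed, because the article gives no ICC for these outcomes: 0 to 0.10.

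**Step 1: reproduce the plan's own figure.** With m patients per department:

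- Design effect = 1 + (m − 1) × ICC = 1 + 25 × 0.05 = 2.25.
- r = [m × ICC × CAC + (1 − ICC) × IAC] / design effect = (26 × 0.05 × 0.5 + 0.95 × 0.6) / 2.25 = 1.22 / 2.25 = 0.542, so 1 − r² = 0.706.
- Variance = (0.3 × 0.7 + 0.5 × 0.5) × 2.25 × 0.706 / (6 × 26) = 0.00468; standard error 0.0684; 0.20 / 0.0684 = 2.92.
- Power from the noncentral t: 79.4% with 20 df, 79.8% with 22 df (75.0% with 10 df; the article does not state the df).
- Attrition: 26 / 0.8 = 32.5, rounded up to 33; 33 × 12 = 396.

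The stated 80% and 396 are reproduced, so the design effect used next is consistent with the plan's own calculation.

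**Step 2: type I error of the chi-square test.** Under no effect, the true variance of the difference is the design effect times the variance the test uses. Hence:

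true error = 2 × [1 − Φ(1.96 / √(1 + (m − 1) × ICC))]

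| ICC | Design effect, m = 26 | Error | Design effect, m = 33 | Error |
|---|---|---|---|---|
| 0 | 1.00 | 5.0% | 1.00 | 5.0% |
| 0.01 | 1.25 | 8.0% | 1.32 | 8.8% |
| 0.02 | 1.50 | 11.0% | 1.64 | 12.6% |
| 0.05 | 2.25 | 19.1% | 2.60 | 22.4% |
| 0.10 | 3.50 | 29.5% | 4.20 | 33.9% |

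Worked line: m = 26, ICC 0.05: 1.96 / √2.25 = 1.307, error 19.1%. The error reaches 10% at an ICC of about 0.017 (m = 26) or 0.013 (m = 33).

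A beta-binomial simulation (100,000 trials per setting, 6 + 6 departments, true rates 30%, 50% and 70%) agrees. At ICC 0.05 it gives 18.7–19.4% for m = 26 and 22.4–22.6% for m = 33. With a continuity correction the figures are about 16–20%.

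**Step 3: the clustered alternative.** In the same simulation, a t-test on 6 versus 6 department proportions with 10 df holds 4.9–5.2% in every setting. If such a department-level statistic were read against 1.96 rather than t with 10 df, the error would be 2 × P(t₁₀ > 1.96) = 7.8%. A clustered analysis therefore also needs a small-sample correction.

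**Step 4: the role of baseline.** Under the composite's correlations, baseline adjustment would multiply the variance by 1 − r², about 0.71. That is a gain in precision. It does not enter the error rates in Step 2.

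**The case against.** The strongest reply is that the closing sentence of the paragraph already gives both outcomes a department-clustered model, framed on change. The order of a simple comparison and a model for non-key secondary outcomes is often settled in an analysis plan, and that plan is not shown. This stands in part: a reader might infer that these outcomes will be judged on the chi-square test alone, and the article does not say so. But the chi-square test is the one named specifically for these two outcomes, and it is not called descriptive. An analysis plan that follows this text inherits it.

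Other points that stand:

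- **ICC.** The value 0.05 belongs to the composite. A reader might infer error several times nominal without condition; at ICC 0.01–0.02 it is 1.6–2.5 times.
- **Cluster size.** The 26 is the planned number after 20% loss. The 33 applies if patients with missing outcomes are counted as failures. Data analysis extends its missing-data approach to secondary outcomes without making this clear, so both are shown.
- **Restricted randomisation.** Balancing on sociodemographic factors, HbA1c and cluster size may reduce chance differences between arms and so the inflation. The article gives nothing from which to quantify this.
- **Baseline and timing.** A reader might infer that leaving out baseline answers also raises false positives, or that the test is run at one time point. In a randomised comparison the first costs precision only. The second is not in the text: no time point is given for this test, engagement is a period measure, and it is not established that a baseline engagement value is collected.

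**Conclusion.** Wrong as written, moderate severity. A patient-level chi-square test is not valid for a comparison of randomised departments when outcomes correlate within department, and the planned mixed model does not cure this while precedence is unstated.

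The size is conditional: about 19–22% true error, roughly four times nominal, if the composite's ICC of 0.05 carries over; 8–13% at 0.01–0.02; about 30–34% at 0.10. These figures assume equal cluster sizes and no gain from the restricted randomisation.

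A higher severity is not supported. The outcomes are secondary and not key, no alpha-controlled claim is attached to them, and a clustered estimate is planned for each.

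**What to change.** In Data analysis, state that the department-clustered analysis is the only inferential result for PHC engagement and for confidence in the health system. Specify a small-sample correction suited to 12 clusters, for example t with 10 df on department-level summaries. Delete the chi-square test, or keep the raw proportions by arm as a description without a p value. Where a baseline value of the outcome is collected, adjust for it to gain precision.

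The cost is wording in the protocol and analysis plan. No change is needed to data collection, sample size or conduct.
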